#### Intervention description

The standard EMDR protocol is difficult to use with people with intellectual disabilities because the eye movement exercises (or alternative bilateral stimulation procedures) are unfamiliar, and their purpose is difficult to explain. However, the procedure can be made more accessible for people with intellectual disabilities and acceptable to therapists by expanding the introductory PES phase and using some of the techniques developed for use with traumatised children (but adapted so as to be appropriate for adults).^45^ Some case study reports suggest that adapted EMDR protocols can be used to treat PTSD in people with intellectual disabilities.^32 33^ However, in our experience, therapists do not feel comfortable using the standard EMDR protocol with people with intellectual disabilities, as clients find it difficult to understand the rationale and the terminology and to manage the desensitisation and reprocessing stages.^46^ We also find that people with intellectual disabilities need extensive preparation before commencing EMDR in order to increase engagement (distrust of services and not being listened to being common experiences) to ensure that they have sufficient understanding of what they need to do, and why, and to militate against dropout from the EMDR phase.

This trial will therefore use a bespoke EMDR protocol that includes, as phase 1, a PES module that aims to instal strengths and resources, stabilise emotional regulation, and build alliance and trust,^40^ and in phase 2 incorporates elements of the EMDR protocol as adapted for children,^47^ with some changes to make it age appropriate for people with intellectual disabilities.

Phase 1 is a 10-session PES protocol that has been previously adapted for people with intellectual disabilities from a PES protocol used routinely with patients with PTSD in some adult mental health services.^48^ Both therapists and people with intellectual disabilities in treatment find PES acceptable. Participants have previously provided positive feedback about their experiences of taking part in our PES protocol.^48^ Although piloted in a group format, the PES module can readily be delivered on an individual basis.^48^ For the purposes of this trial, the PES module was further adapted by including an introduction to bilateral stimulation.

We have also previously piloted a modified phase 2 EMDR protocol.^46^ The major adaptations^45^ are (1) making the stages, language and outcomes more accessible; (2) not preferring side-to-side finger movements over other forms of bilateral stimulation such as tapping; (3) encouraging creative use of expression (such as techniques from art and narrative therapy/storytelling eg,^47^ and (4) involvement of carers where appropriate to support the patient within and/or between therapy sessions.

The intervention is fully manualised. The PES phase comprises 10 weekly sessions which can be extended if required, while the EMDR phase also comprises 10 sessions but can be extended to 14 sessions if required.

Within each trial site, therapists have been trained to deliver PES/EMDR. Training comprised the standard accredited training (previously known as levels 1 and 2 and currently known either as parts 1–3 or parts 1–4). It followed the standard training curriculum split over two blocks to include a further day on our adapted protocol and a final training day following 4–6 months of supervised practice. It is equivalent to standard EMDR accredited training. In light of experience in the early stages of the trial, and in line with the national EMDR training curriculum, therapists are encouraged to undergo 1 month of supervised practice. For a minority of therapists who had previously been trained to deliver EMDR, only the training in our adapted protocol was delivered. All therapists also undertook training on remote delivery of EMDR, comprising a 1-day workshop and access to remotEMDR software (https://www.remotemdr.com/). Additional refresher training was available for sites that experienced significant delays in starting due to COVID-19. The therapists subsequently have access to supervision sessions via MS Teams in small groups, with additional phone supervision available as needed.

#### Criteria for discontinuing or modifying allocated interventions

A participant or their carer may terminate their participation in the trial at any time without giving a reason and with no personal disadvantage. Participants allocated to PES/EMDR may wish to terminate treatment. If this occurs, participants will be invited to remain in the trial and provide outcome data. Trial participants may also be withdrawn by the study team due to serious adverse events (eg, hospitalisation, serious illness, death). The sponsor has the right to terminate this trial at any time. In terminating the trial, the sponsor and the chief investigator will ensure that adequate consideration is given to the protection of trial participants. If the trial is suspended or terminated for safety reasons, the sponsor will promptly inform the chief investigator. The sponsor will also promptly inform the relevant regulatory authorities of the suspension/termination and of the reasons for this action, including the Trial Management Committee and Data Monitoring and Ethics Committee.

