### Sample size

A total of 144 patients will be recruited to the main trial. We aim to detect a medium-to-large effect size (ES) of 0.65, with two-tailed significance at α=0.05 and power=0.90. This requires N=102 independent outcomes, equivalent to N=108 analysable outcomes from small clusters (average of 4 participants per therapist) with an intracluster correlation of 0.02. Our recruitment target thus pragmatically allows for both 25% loss to follow-up and (hitherto unreported) therapist effects in EMDR for PTSD.

A meta-analysis of studies of EMDR versus TAU in the general adult population reported a mean ES=1.17 with 19% loss to follow-up;^16^ a second meta-analysis, restricted to studies of survivors of childhood abuse, which many of our participants are expected to have experienced, reported a smaller ES=0.76.^61^ The mean across these two studies=0.97. For trials of CBT (the only intervention type for which there exists a corpus of information for people with intellectual disabilities), effect sizes for people with intellectual disabilities are small and biased.^25^ The ES used here in sample size considerations is a conservative two-thirds of the mean figure for the two meta-analyses cited.

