### Statistical methods for primary and secondary outcomes

#### Quantitative outcomes

The primary outcome will be assessed using an intention-to-treat analysis. Quantitative outcome measures will be analysed by analysis of covariance, adjusting for baseline values of the outcome and any variables used in the randomisation process. Secondary outcomes will be analysed using linear or logistic regression models as appropriate reflecting the distribution of the outcome variable. The treatment effect will be estimated as an adjusted difference between sample means, presented with 95% CIs and p values. A statistical and health economic analysis plan (SHEAP) will be produced and finalised before data lock.

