#### Methods in analysis to handle protocol non-adherence and any statistical methods to handle missing data

Every attempt will be made to minimise missing data, including follow-up of participants who discontinue treatment. Patterns and levels of missing data will be assessed. Procedures will be in place for validating all data and imputation will be considered if required.

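### Withdrawal of participants by the study team after serious adverse events carries no continued outcome or cost collection, which conflicts with the intention-to-treat analysis

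*Protocol article*

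**What the plan says.** The protocol article's section on criteria for discontinuing or modifying allocated interventions deals with two groups. Participants in the PES/EMDR arm who wish to end treatment are asked to stay in the trial and supply outcome data. For SAEs the text reads: "Trial participants may also be withdrawn by the study team due to serious adverse events (eg, hospitalisation, serious illness, death"). Nothing is said about outcome collection for this second group.

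The section on quantitative outcomes says: "The primary outcome will be assessed using an intention-to-treat analysis". The abstract says the same. The sample-size section states: "Our recruitment target thus pragmatically allows for both 25% loss to follow-up". On missing data, the protocol says that patterns will be assessed and that "imputation will be considered if required". The section on health economic outcomes places the service-receipt inventory (CSRI-ID) at baseline and at 14 months; Table 1 marks additional collection during the two treatment phases.

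**The concern.** Intention-to-treat means that participants are followed and analysed as randomised, whatever happens afterwards. A rule that lets the team end someone's participation because of a bad clinical event after randomisation works against that. Hospitalisation and serious illness can be related to PTSD symptoms and general mental health, so the people removed may be doing worse than those who stay. If removal differs between arms, the comparison is distorted. The same people are likely to carry high service costs. Under the health-economics text, someone withdrawn after an admission would give no CSRI-ID after baseline. An analysis plan can choose how to handle missing scores, but it cannot recover data that were never collected.

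**Working it through.** **1. What the text covers.**

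| Group | Section of the protocol article | Continued outcome collection stated? |
|---|---|---|
| Participant chooses to stop PES/EMDR | Criteria for discontinuing or modifying allocated interventions | Yes |
| Participant discontinues the intervention | Plans to promote participant retention and complete follow-up | Yes, attempted |
| Participant discontinues treatment | Methods to handle non-adherence and missing data | Yes |
| Participant withdrawn by the study team after an SAE | Criteria for discontinuing or modifying allocated interventions | No |

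The section heading concerns interventions. The SAE sentence, however, is about participants in the trial, applies to both arms, and follows directly on a sentence about staying in the trial. Withdrawal from the trial is the natural reading.

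**2. Is the loss avoidable?** For hospitalisation and serious illness, often yes. The trial recruits from hospital as well as community services (Abstract, Trial setting), and assessments may be spread over several sessions (Plans for assessment and collection of outcomes). Admission therefore does not in itself prevent assessment. Death does.

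**3. The plan's own figures.** The sample-size section takes a standardised effect of 0.65, a two-sided 5% test, 90% power, clusters of 4 per therapist and an intracluster correlation of 0.02. Its stated result is: "This requires N=102 independent outcomes, equivalent to N=108 analysable outcomes from small clusters (average of 4 participants per therapist").
- Two-sample t-test, d = 0.65: 50.7, so 51 per arm, total 102. The normal approximation gives 50 per arm.
- Design effect: 1 + (4 − 1) × 0.02 = 1.06; 102 × 1.06 = 108.1, stated as 108.
- Allowance for loss: 108 / 0.75 = 144.

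All three figures reproduce. The calculation tolerates 144 − 108 = 36 participants without an analysable outcome. That protects power; it gives no protection against outcome-related loss.

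**4. Size of the possible shift.** Let f be the share of an arm lost and k the number of SDs by which those lost are worse than their full-arm mean. The observed arm mean then looks better by f × k / (1 − f), and the shift in the treatment difference is the PES/EMDR term minus the TAU term. The documents give neither f nor k, so both are assumed. For a baseline-adjusted analysis, k is the part not explained by the covariates.

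| Lost, PES/EMDR v TAU | k = 0.5 | k = 1.0 | Share of 0.65 |
|---|---|---|---|
| 5% v 0% | 0.026 | 0.053 | 4% to 8% |
| 10% v 5% | 0.056 − 0.026 = 0.029 (unrounded inputs) | 0.111 − 0.053 = 0.058 | 4% to 9% |
| 10% v 0% | 0.056 | 0.111 | 9% to 17% |
| 10% v 10% | 0 | 0 | 0 |
| 5% v 10% | −0.029 | −0.058 | −4% to −9% |

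Positive values favour PES/EMDR. With 72 per arm, 10% is about 7 people.

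**The case against.** The strongest reply is that the heading concerns allocated interventions, so the sentence may mean only that therapy stops. The wording is permissive, one of its three examples is death, and nothing says that earlier data are discarded or that the person leaves the analysis set. The sizes above rest on assumed rates. Even the largest, 0.11 SD, is below one standard error: with 108 analysable outcomes, design effect 1.06 and an assumed baseline correlation of 0.5, the standard error is √(4 × 1.06 / 108 × 0.75) ≈ 0.17 SD.

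Much of this stands. The text is ambiguous and the likely shift is modest. But the ambiguity is itself what needs correcting, because sites act on this wording while follow-up is running.

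A reader might also infer more than the documents support:
- **That the primary analysis is a complete-case ANCOVA at one visit.** No section says so. The visit for the primary analysis is not named in the statistical methods; 14 months (60 weeks) appears in the subgroup and health-economic text. Imputation is left open, and detail is deferred to a statistical and health economic analysis plan (SHEAP) that is not shown.
- **That 25% loss is expected.** It is a planning allowance.
- **That preventing admission is a stated aim.** The background names admission as a risk in this population; the risks-and-benefits section does not list avoiding it as a benefit.
- **That unmasked staff would decide, or that the bias favours PES/EMDR.** The clinical team cannot be blinded, but who within the study team decides is not stated, and nothing fixes which arm would lose more.

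**Conclusion.** The point holds as a defect in one stated rule. Participants with an SAE may be withdrawn with no provision for further assessment, while those who stop therapy are kept in, and no other section closes the gap. On its natural reading the rule is at odds with the intention-to-treat analysis and could remove outcome-related cases, together with their 14-month CSRI-ID costs.

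The size cannot be fixed from the document. Under assumed unequal loss of 10% v 5% or 10% v 0%, with those lost 0.5 to 1 SD worse, the shift is about 0.03 to 0.06 SD or 0.06 to 0.11 SD. It is nil if loss is equal and alike, and changes sign if TAU loses more. The effect on costs cannot be quantified. The choice of ANCOVA is not shown to be wrong, and the sample size of 144 is unaffected.

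**What to change.** Amend the section on discontinuing or modifying allocated interventions in two ways:
1. Separate stopping the intervention from leaving the trial.
2. State that an SAE does not end outcome or cost collection, and does not remove the participant from the analysis set, unless consent is withdrawn or the participant dies. Align the retention and missing-data sections with this.

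Whether therapy continues after an SAE is a clinical matter and is not addressed here.

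The cost is a short amendment that needs sponsor and ethics committee approval. The trial-status section says recruitment closed on 31 December 2024 and follow-up is continuing, so the change can help only assessments still outstanding. Any participants already withdrawn under the present wording should be reported by arm, with reasons.

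As an option for the SHEAP, and not as a correction of an error, the 14-month analysis should use the 4- and 8-month IES-ID scores already collected, through a likelihood-based repeated-measures model or multiple imputation. Either is somewhat more complex and still assumes that data are missing at random.

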#### Fidelity and adherence

Fidelity of treatment delivery will be monitored from encrypted audio recordings of PES and EMDR sessions. For each therapist, one session from each phase will be recorded—with participant consent. Assessment of the PES session will be made using the Trauma-AID PES Intervention Checklist. Some generic items in the checklist were adapted from the Manualised Group Intervention Check;,^49^ a 30-item monitoring instrument for group CBT adapted for people with ID. Additional items were incorporated to reflect manual-specific activities and processes in the PES stage to produce an 18-item checklist that addresses engagement skills, accessibility of presentation, understanding, session content, establishing internal safety/emotional stabilisation and developing adaptive coping/preparation for reprocessing. Assessment of the EMDR session will be made using the Fidelity Checklist for Trauma-AID EMDR Sessions, a 21-item checklist incorporating items adapted from the EMDR Fidelity Rating Scale Version 2^50^ as well as manual-specific items. The checklist covers treatment planning and assessment; preparation; calm place exercise, skills and resources; assessment (ahead of trauma confrontation); desensitisation; installation and closure; and future templates. Each recording will be rated by a senior member of the research team, who is familiar with the manualised intervention, using the appropriate checklist. To examine inter-rater reliability, a second rater, who is an expert in EMDR (CC), will double-rate 15% of the recordings. The sample for dual assessment will be randomly selected.

At the end of each session, therapists complete a Clinical Trials Unit online form to report whether the participant attended the session. The therapist also reports the goals for the session and whether or not they were achieved.

#### Relevant concomitant care permitted or prohibited during the trial

Participants can receive any concomitant care considered suitable by their clinical team other than another trauma-focused psychological therapy.

#### Provisions for post-trial care

As participants are treated by clinical services to which they have been referred, those services will remain responsible for post-trial care. Participants will have access to normal NHS complaints and compensation procedures. No special procedures are used.

### Outcomes

#### Primary outcome

PTSD symptoms. The self-report revised Impact of Event Scale–Intellectual Disabilities (IES-IDs)^6^ is our primary outcome measure. We use the IES-IDs rather than the Clinician Administered PTSD subscales^51^ because the IES-IDs have been adapted and tested for use with people with intellectual disabilities.^6 39^

#### Secondary outcomes

PTSD symptoms. The self-report ITQ-ID 39 and the informant-version Lancaster and Northgate Trauma Scale^7 52^.Mood. The self-report Glasgow Depression and Anxiety Scales ^53 54^ and Clinical Outcomes in Routine Evaluation–Learning Disability.^55^Mental Health. Carer ratings of the participant’s mental health (MPAS-ID)^56^ and challenging behaviour, the Aberrant Behaviour Checklist.^57^Health-Related Quality of Life (QoL). This is assessed using the self-reported well-being using the Personal well-being Index–Intellectual Disability (PWI-ID)^58^ and carer reports using the Short Form Health Survey (SF-12).^59^ The SF-12 is a standard, well-validated instrument. The PWI-ID is well-validated in general populations and as well as for people with intellectual disabilities. We have included this measure because we feel it is important to attempt to evaluate QoL as experienced by the participants themselves.Carer burden. The Warwick-Edinburgh Mental Well-being Scale (WEMWBS).^60^

All outcome measures are completed at baseline and at 4, 8 and 14 months postrandomisation.

### Participant timeline

Our participant schedule of events and schedule of outcome assessments is found within table 1.

**Table 1 T1:** Schedule of events and outcome assessments

	Study period							
	Referral/clinic prescreening* (≤12 weeks)	Screening (<4 weeks)	Baseline Week 0	Phase 1 (PES/TAU) Weeks 5–16		Phase 2 (EMDR/TAU) Weeks 17–27		Follow-up Week 60
Week	**≤–12**	**–4**	**0**	**5–15**	**16**	**17–27**	**28**	**60**
Participant and carer								
Clinical history	Y							
Patient information	Y							
Participant								
Consent		Y						
Diagnostic interview		Y						
Diagnostic review		Y						
Concomitant medication		Y		Y	Y	Y	Y	Y
Confirm eligibility		Y						
Randomisation			Y					
Treatment (1–10 sessions for phase 1 and phase 2)				Y	Y	Y	Y	
Adverse events				Y	Y	Y	Y	Y
Subjective Units of Distress Scale (SUDS)				Y	Y	Y	Y	Y
IQ (WASI-II)		Y						
PTSD History (TIF)		Y						
PTSD Diagnosis/Complexity (ITQ-ID)		Y		Y	Y	Y	Y	Y
Self-reported questionnaires*†			Y		Y		Y	Y
Carer								
Adaptive Behaviour Assessment System - III (ABAS-III)		Y						
Carer-reported questionnaires‡			Y		Y		Y	Y
Self-reported questionnaires§			Y		Y		Y	Y
Service/Support Costs (CSRI-ID)			Y	Y		Y		Y
Audio recording	With participants' consent, one treatment session from phase 1 and phase 2 will be recorded with scoring using the EMDR Fidelity Rating Scale							
Interview	In line with qualitative recruitment methods, around 10 each of patients, carers and therapists will be interviewed about their experiences following completion of therapy.							

All visits are anticipated to take place in clinic or community settings, although other scenarios are permissible as required

* Completed assessments must be within 12 weeks of screening

† Patient completed self-reported questionnaires consist of IES-ID, GDS, GAS, PWI-ID

‡ Questionnaires completed by the carer regarding the participant: MPAS-ID, LANTS, ABC.

§ Questionnaires completed by the carer about their own well-being: SF-12, WEMWBS

ABC, Aberrant Behavior Checklist; CSRI-ID, Client Service Receipt Inventory– Intellectual Disabilities; EMDR, eye movement desensitisation and reprocessing; GAS, Glasgow Anxiety Scale; GDS, Glasgow Depression Scale; IES-ID, Impact of Event Scale–Intellectual Disabilities; ITQ-ID, International Trauma Questionnaire–Intellectual Disabilities; LANTS, Lancaster and Northgate Trauma Scales; PES, psychoeducation and emotional stabilisation; PTSD, post-traumatic stress disorder; SF-12, Short Form Health Survey; TAU, treatment-as-usual; WEMWBS, Warwick-Edinburgh Mental Well-being Scale.

### Sample size

A total of 144 patients will be recruited to the main trial. We aim to detect a medium-to-large effect size (ES) of 0.65, with two-tailed significance at α=0.05 and power=0.90. This requires N=102 independent outcomes, equivalent to N=108 analysable outcomes from small clusters (average of 4 participants per therapist) with an intracluster correlation of 0.02. Our recruitment target thus pragmatically allows for both 25% loss to follow-up and (hitherto unreported) therapist effects in EMDR for PTSD.

A meta-analysis of studies of EMDR versus TAU in the general adult population reported a mean ES=1.17 with 19% loss to follow-up;^16^ a second meta-analysis, restricted to studies of survivors of childhood abuse, which many of our participants are expected to have experienced, reported a smaller ES=0.76.^61^ The mean across these two studies=0.97. For trials of CBT (the only intervention type for which there exists a corpus of information for people with intellectual disabilities), effect sizes for people with intellectual disabilities are small and biased.^25^ The ES used here in sample size considerations is a conservative two-thirds of the mean figure for the two meta-analyses cited.

### Recruitment

The research team meets regularly with principal investigators (PIs) in each of the participating Trusts, and the PIs ensure that their colleagues within clinical psychology and the wider clinical team are alert to opportunities to put forward potential candidates for screening. The recruitment process is overseen by a field coordinator who has close relationships with all PIs. Patients who are newly referred to the service or those on waiting lists will be screened for eligibility to take part.

